## Abstract

**Background:**

The global prevalence of type 2 diabetes is considerable. To avoid or delay its chronic complications, patients with type 2 diabetes should improve blood glucose management by adapting their life style. This involves changing the way in which diabetes is controlled. We believe that, thanks to technological innovations in connected health-monitoring devices, the telemonitoring of type 2 diabetes patients using therapeutic educational tools is likely to help them adapt their treatment and lifestyle habits, and therefore improve blood glucose management.

**Methods:**

This is a multicenter, randomized, controlled, prospective study. The primary objective is to compare the efficacy of telemonitoring to standard monitoring in terms of changes in glycated hemoglobin levels (HbA1c) after a 1 year follow-up period. The secondary objectives are clinical (changes in knowledge, physical activity, weight, etc.) and medical-economic. 282 patients are required (141 patients in each group) to satisfy the primary objective. For patients in the intervention group, the device will be given to them for 1 year and then withdrawn during the second year of follow-up.

**Conclusions:**

The anticipated benefits of this research are an improvement in blood glucose management in patients with type 2 diabetes by improving their lifestyle whilst rationalizing recourse to consultations in order to reduce the incidence of complications and cost in the long term. If the results of this study show that management of type 2 diabetes by tele monitoring is clinically effective and economical, this device could then be made available to a larger diabetic patient cohort.

## Background

According to the World Health Organization (WHO), 422 million people suffer from diabetes world-wide. This qualifies as a genuine pandemic since progression is considerable. Thus the WHO is forecasting that 622 million people will be suffering from diabetes between now and 2040 [1]. Over 90% of these people present type 2 diabetes. The severity of diabetes, from both a human and economic perspective, is the onset of chronic complications associated with the disease. To avoid or delay their onset as much as possible, patients with diabetes must improve the way in which they manage their blood glucose levels. Type 2 diabetes patients can be treated in different ways, depending on disease advance, ranging from a change in lifestyle alone, oral treatments or multiple insulin injections, or a combination of all options. The French Health Authorities (HAS) continue to advocate the following first-line therapy: a change in lifestyle with a change in diet and regular physical exercise for improved blood glucose management together with weight loss, if applicable [2, 3]. These measures must be maintained long-term even when combined with medication. Numerous studies have shown that a change in lifestyle can improve patients’ blood glucose levels but long-term results are difficult to maintain [4–6]. Thanks to technological innovation, health-related devices can now be used to monitor patients remotely in their own homes and play a greater role in daily routines by helping patients to improve their lifestyle and adjust their treatment [7–12].

We want to compare telemonitoring management incorporating therapeutic education tools for type 2 diabetes with standard monitoring. We believe that this telemonitoring management approach will improve patients’ blood glucose levels, lifestyle and quality of life whilst rationalizing recourse to consultations, thus helping to reduce the incidence of complications and long-term costs.

### Study objectives

The main objective is to compare the efficacy of telemonitoring versus standard monitoring in terms of changes in glycated hemoglobin (HbA1c) levels after a follow-up period of 1 year. Secondary objectives are changes in knowledge (evaluated using questionnaires focusing on dietetics and physical activity—GPAQ), hygiene and dietary approaches (3-day dietary questionnaires including 1 day at the weekend), quality of life (EQ 5D and DQOL questionnaires), clinical (weight, waist circumference) and laboratory parameters (lipid and mean glycemic fractions). These parameters are evaluated at baseline and after 1 year of follow-up. Patient and care satisfaction is also assessed after 1 year with continued efficacy (HbA1c) at 2 years. A medical-economic evaluation is also carried out and assessed after 1 and 2 years, respectively (cost-efficacy ratio, Markovian modelling for the longer term forecasting of medical and economic consequences).

Secondary objectives, specifically for patients in the intervention group are combined with the use of connected devices. They are defined to describe changes; in diet, in nutritional knowledge, in the extent to which physical exercise is carried out, in weight and body composition, in mean blood glucose levels and patient acceptability of the device.

### Study design

A multicenter, open-label, randomized controlled trial in patients has been carried out with type 2 diabetes patients, comparing an intervention group with the telemonitoring device under study versus a control group based on standard monitoring.

The study procedure is summarized in Fig. 1.

**Fig. 1 Fig1:**
[figure not shown]
Study design and schedule. Comparative, randomized, open, multicenter intervention trial with parallel-group evaluating a telemonitoring program for patients with type 2 diabetes, whose glycemic control can be improved, compared to a traditional optimized care. Patients are recruited during therapeutic educational sessions or appointments by general practitioners or diabetologists. If patients accept to participate to the study and sign up the protocol consent, they are randomized into two groups: one arm is trained to the telemonitoring device before receiving it at home, and the other arm keeps usual care. During 12 months, the intervention group uses the device, and health teams use the web platform to follow the measured parameters and to make appropriate decisions about health care of their patient. Biomedical and economic data are collected along the study to assess medical and cost impact of the device between the two arms

## Methods

### Methods: participants, intervention and outcomes

#### Study setting

This study includes 16 patient recruitment investigating centers located throughout France: 5 university hospitals, one non-university medical center, a diabetology treatment network comprising 8 public and private health establishments and 2 independent physicians.

#### Inclusion and non-inclusion criteria

The patient inclusion and non-inclusion criteria are presented in Table 1.

**Table 1 Tab1:** Patient’s inclusion and non-inclusion criteria

Inclusion criteria
Patient with type 2 diabetes
Patient over 18 years of age
Presenting blood glucose profile characterised by HbA1c levels ranging from >6.5 to 10%
With and without insulin
Having an internet connection at home
Agreeing to the training methods and to hire and use the device
Belonging to a social security system
Having given his/her informed consent and having signed the consent form
Non-inclusion criteria
Subject with reduced mobility
Subject living in an institution
Women wishing to have a baby, pregnancy, breast-feeding
Person participating in another clinical trial
Person placed under a legal protection system
Serious disease of recent onset (<3 months) or decompensated disorder likely to affect the patient’s blood glucose management in the long term
Confirmed haemoglobinopathy
Visual, intellectual or physical impairment
Inability to understand all or some of the software information
Retinal status not permitting optimisation of blood glucose management
Confirmed severe renal impairment (creatinine clearance <30 ml/min)
Person with severe dietary disorders
Person having undergone or about to undergo bariatric surgery
Person with an implanted electronic medical device

#### Intervention

Subjects are recruited from several investigating centers. After obtaining an informed consent, clinical examination is performed by the physician and questionnaires are collected. Patients are randomized into two groups: one arm is trained by the research staff on the telemonitoring device before receiving it at home through a demonstration device to familiarize with the connected objects. Instructions for use and the phone number of the project team are given to patients. Within 15 days a specialist in Health equipment, previously formed, comes in the patient home to install the device and explain to them the operation if necessary.

A hotline managed by our service provider is also available to patients to prevent them from experiencing technical or operational issues.

During 12 months, the intervention group uses the device, and health teams use the web service to follow the measured parameters and to make appropriate decisions about health care of their patients. Biomedical and economic data are collected along the study to assess medical and cost impact of the device between the two arms.

The other arm keeps usual care (Fig. 1).

#### Telemonitoring device (Fig. 2)

Tele-monitoring device available for use by type 2 diabetes patients in their own homes includes three educational software applications [13–15] focusing on a balanced diet and physical activity, available on tablets, and biomedical data sensors (scales with impedancemetry, actimeter, blood glucose monitor).

**Fig. 2 Fig2:**
[figure not shown]
Telemonitoring devices available for the patient at home. A telemonitoring device with educational tools is given to people with type 2 diabetes at their home. It is composed of three software applications available on a tablet to improve eating habits, a self-monitoring blood glucose device, a connected scale to measure weight and fat mass, and a pedometer to evaluate physical activity. Secured web services are used to send and store data and to deliver a synthesis to patients and health professionals

##### Educational software

Patients in the telemonitoring arm will have a tablet at home which they can use to access 3 interactive educational software applications: Nutri-Educ, Nutri-Kiosk and Acti-Kiosk.

Nutri-Educ is a personalized nutritional educational software application that meets international clinical trial recommendations [16]. It allows patients for whom a profile and nutritional requirement record has been created to enter their meals (in the form of photos with various portions of food), to establish whether or not their meals are balanced and to obtain one or more suggestions for improving the nutritional balance (Fig. 3). These meals can be recorded and used in the patient telemonitoring process. Based on feedback from the teaching units in our department of Diabetology, we assessed that asking for the description of six meals per month is the most feasible.

**Fig. 3 Fig3:**
[figure not shown]
An example of meal with a proposition of correction to improve the nutritional balance. Nutri-Educ is an interactive, educational, nutrition software application that provides personalized help in the composition of meals. Each user has a personalized folder that contains some of its physiopathological characteristics. It was developed by the department of Diabetology of the University Hospital of Toulouse in collaboration with a computer engineer. It has several features: the system evaluates the energy needs of the subjects by a set of rules, taking into account age, sex, size, physical activity. The caloric goal is then adapted according to the BMI of the subject. It helps the user to balance his meals with personalized advice. It takes into account the daily fractionation of the feed. The user enters the foods that make up his/her meal with photos to choose the type of food and its portion. Nutri-Educ makes a diagnosis of the meal calorically and on the carbohydrate-lipid-protein distribution according to the international recommendations. It mentions the lack of fiber, calcium… and then indicates several food combinations involved in the imbalance of the meal. It is able to offer balanced meal solutions from the foods seized by the user while trying to respect the choices of the subject as well as possible

Patients are asked to enter 2 breakfasts, 2 lunches and 2 dinners per month as a minimum requirement. Nutri-Kiosk is a series of quizzes which test patients’ nutritional knowledge. EDUC@DOM patients are advised to use it at least once a month.

Acti-Kiosk is a software application that allows patients to assess their physical activity/sedentary behavior. It gives tips on how to start up a physical exercise program (warm-ups, stretching, adjusting the bicycle saddle, etc.) in the form of videos.

##### Connected health devices

In addition to these education software applications, connected health devices form part of the telemonitoring system: connected blood glucose monitor to record blood glucose readings taken by patients, a connected scale with impedancemetry to monitor weight (with fat mass and lean mass) and an actimeter to monitor physical activity (number of steps taken, climbing stairs or hills, intensity of the activity). Some of the connected devices such as the scales do not require any intervention on the part of the patient to send the data, whilst others require data to be downloaded (blood glucose monitor) or the device has to be positioned next to the tablet (actimeter). Patients are asked to submit their data once a week.

##### The web telemonitoring platform

All of these data are sent to a secure web platform. A software application translates these data in the form of graphs and charts to produce a summary that can be accessed by the doctor and by the patient via the tablet, on request. This summary (Fig. 4) includes an initial display of data over the last 30 days (weight, number of steps taken, intensity of the physical activity, targets in the form of benchmarks for meals, blood glucose diary) with a month-by-month average of the various follow-up parameters. All of the meals entered by the patients can also be accessed.

**Fig. 4 Fig4:**
[figure not shown]
Remote monitoring report summarizes the important parameters of diabetes. A module on the tablet will synthesize all of this information and provide an assessment to the patient at the time of his choice in the form of tables and graphs: weight curve, evolution of pre- and postprandial glycemic averages, Physical activity (number of steps recorded by the actimeter, number of stages assembled, time of physical inactivity), evolution of dietary behavior (evolution of caloric intake and quality of nutrients (calories, carbohydrates, lipids, proteins…). This module will send technical alerts to the project team if the tools are not used. A module available on a secure server will store and synthesize this data and make it available to caregivers (general practitioners, diabetologists, and dieticians) in monthly synthesis form. They will be able to see this synthesis which will enable them to refocus their objectives relative to patients in a personalized way

Using this platform, the investigators can also access the patient record and can amend the targets initially predicted at the inclusion visit that patients have to reach over time: number of steps, blood glucose targets or weight. These objectives are also viewable by the patient in the summary at any time.

In the intervention group, patients are remotely monitored for the first year and are then followed up according to standard procedure in the second year. No consultation is scheduled in advance during the telemonitoring year. Consultations can take place at the request of doctors or patients, if required. An e-mail is sent to investigators once a month to remind them to remotely monitor their patients. Medical alerts are programmed and can be adapted for individual patients and e-mailed to investigating physicians with a link to connect to the monitoring platform. These alerts highlight hypoglycemia with cases of hyperglycemia accounting for over 30% of the blood glucose levels recorded, and excessive weight loss or weight gain.

In this study a hypoglycemia alert is triggered when the patient’s blood glucose level is under 3.3 mmol/l (59.45 mg/dl) and a hyperglycemia alert is triggered when the patient’s blood glucose level is over 8.8 mmol/l (160 mg/dl). However, these thresholds are modular and can be adjusted by the physician according to the patient profile.

These alerts should not be viewed as emergency cases but provide investigators with information on events over the last 15–30 days. There is no procedure to follow the physician judge the therapeutic action to be brought.

The project team receives technical alerts by e-mail. These technical alerts inform the project team if patients have not connected to the system for more than 15 days. In response, they contact the patients via the platform e-mailing system or by telephone to resolve any technical problems provide advice or motivate patients.

##### The secure messaging system

A secure messaging system facilitates patient contact and coaching.

The physician according to the telemonitoring sends messages to patients for coaching.

Patients can choose the receiver of the message depending on the nature of the request (medical or technical).

##### The telemonitoring report

Investigators are asked to provide a telemonitoring report in the form of a pop-up menu. They are required to sign the telemonitoring document and provide an estimate of the amount of time spent on telemonitoring from a medical-economic standpoint.

#### Outcomes

The primary endpoint is the difference between HbA1c level after 1 year of follow-up and the targeted HbA1c level defined at baseline by the physician in charge of the patient (based on the recommended strategy for glycemic control in type 2 diabetes) [17, 18]. HbA1c levels are measured by high-performance liquid chromatographic (HPLC) methods HbA1c levels will be measured at baseline, 3, 6, 9 and 12 months of follow-up.

The secondary outcomes are:

Comparison between the two arms for assessment at baseline and after 1 year of follow-up of:Improvement of nutritional knowledge, questionnaires will be given to patients.Dietary intake measured by a validated food survey based on 3-day food record.Physical activity practice, measured by the general physical activity questionnaire (GPAQ.Body composition, BMI (body mass index), waist circumference will be measured.Mean of blood glycaemia, self-monitoring blood glucose books will be copied.Total cholesterol, triglycerides and high density lipoprotein (HDL) cholesterol blood levels, a blood sample will be collected.Quality of life of patients, measured by the diabetes quality of life questionnaire (DQOL) and the EQ-5D questionnaires.

Direct and indirect costs will be recorded at baseline, throughout the study and at the closure visit. The economic analysis will be carried out from the cost payer’s point of view, Assurance Maladie (Health Insurance). Direct medical costs (directly attributable to patient treatment), direct costs of a non-medical nature (travelling expenses and the costs incurred through implementing the telemonitoring programme) and indirect costs (production losses) to be paid by health insurance, mutual insurance and patients will be calculated.

Specifically for the intervention group, assessment of the evolution of parameters collected with the telemonitoring device.Food behavior through meals registered with the Nutri-Educ software.Nutritional knowledge through rate of good choices playing games of Nutri-Kiosk software.Physical activity measures collected with the podometer (number of steps, number of stairs climbed up and intensity).Weight, fat rate and lean rate collected with the balance.Means of glycaemia collected with the self-monitoring blood glucose device.Acceptability and satisfaction of the telemonitoring system by the patients with the number and time of connections during the 1st year of follow-up and a questionnaire at 1 year.Acceptability and satisfaction of the telemonitoring system by the health professionals with the number and time of connections leading to a medical decision (phone call or medical appointment) during the 1st year of follow-up and a questionnaire at 1 year.

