##### Primary outcome analysis

The primary outcome (difference between HbA1c level after 1 year of follow-up and baseline targeted HbA1c level) will be compared between the two groups. The difference between the the intervention and control groups will be assessed firstly using bivariate analysis (Student’s T test), and secondly using mixed model analysis for repeated measures. The mixed model will be adjusted for the baseline value of HbA1c, as well as additional baseline variables that might be potential confounders: center, age, gender, treatment by insulin, duration of diabetes and history of diabetes complications. To manage missing data, a sensitivity analysis using the last observation carried forward (LOCF) technique will be applied. Secondary outcomes will be analyzed according to the same principles. A bivariate analysis will be computed, followed by a multivariate analysis of covariance (ANCOVA) adjusted for the baseline value of the corresponding secondary outcome and the same set of potential baseline confounders than in the primary outcome analysis.

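### The primary endpoint subtracts a physician-set HbA1c target that neither the objective, the sample size nor the mixed model takes into account

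*Protocol article*

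**What the plan says.** - **Objective** (Study objectives; the abstract agrees): to "compare the efficacy of telemonitoring versus standard monitoring in terms of changes in glycated hemoglobin (HbA1c) levels after a follow-up period of 1 year".
- **Endpoint** (Outcomes): the HbA1c after 1 year minus "the targeted HbA1c level defined at baseline by the physician in charge of the patient". Primary outcome analysis repeats it: "The primary outcome (difference between HbA1c level after 1 year of follow-up and baseline targeted HbA1c level) will be compared between the two groups". It is therefore not a slip of wording in one place.
- **Analysis** (Primary outcome analysis): the arms are compared "firstly using bivariate analysis (Student’s T test), and secondly using mixed model analysis for repeated measures". On covariates: "The mixed model will be adjusted for the baseline value of HbA1c, as well as additional baseline variables that might be potential confounders". Those named are center, age, gender, insulin treatment, diabetes duration and history of complications. The target is not named.
- **Stratification** (Allocation): baseline HbA1c below 7.5% versus 7.5% or above. The target plays no part.
- **Sample size** (Sample size): Frison and Pocock approach on the mean of the 3, 6, 9 and 12 month measurements, SD 2 points, pre-post correlation 0.4, post-post correlation 0.5, difference 0.5 points, 80% power, two-sided 5%. This gives 117 per arm. No quantity for the target enters.

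**The concern.** The objective, the endpoint and the sample size do not describe the same quantity. The gap between change in HbA1c and HbA1c level is harmless here: once baseline HbA1c is a covariate, both give the same treatment estimate. The target is different, because it is subtracted from the outcome but is not a covariate.

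The between-arm difference in HbA1c minus target equals the difference in HbA1c minus the difference in mean target. A target set at baseline cannot respond to telemonitoring, so a difference in targets between arms carries no information about treatment. The target is also constant within a patient, so four visits do not average it out as they average out visit-to-visit variation. At stake are some precision that the sample size calculation assumes is there, and a primary result that does not directly answer the question as worded.

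**Working it through.** **1. Reproduce the plan's figure.** With one baseline and four follow-up measurements, the baseline-adjusted variance of the follow-up mean is

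V = SD² × [(1 + 3 × 0.5)/4 − 0.4²] = 4 × (0.625 − 0.16) = 4 × 0.465 = 1.86.

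n per arm = 2 × (1.960 + 0.842)² × V / 0.5² ≈ 62.8 × 1.86 ≈ 116.8, so 117, as stated. Two alternatives with the same inputs do not reproduce it: the follow-up mean without baseline adjustment needs 157, and change from baseline to the follow-up mean needs 208. The 117 therefore belongs to baseline-adjusted HbA1c, with no target term.

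**2. Add the target.** Let s be the SD of the target. The article does not give it, so 0.3, 0.5 and 0.7 points are assumed. Suppose first that the target is unrelated to later HbA1c given baseline, and that the other covariates do not predict it. The variance becomes V + s², the 95% half-width is 1.96 × √(2(V + s²)/117), and power is Φ(0.5/√(2(V + s²)/117) − 1.96).

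| Target SD s | V + s² | 95% half-width | Widening | Power at 117 | n per arm for 80% |
|---|---|---|---|---|---|
| none | 1.86 | 0.35 | – | 80% | 117 |
| 0.3 | 1.95 | 0.36 | 2% | 78% | 123 |
| 0.5 | 2.11 | 0.37 | 6-7% | 75% | 133 |
| 0.7 | 2.35 | 0.39 | 12% | 70% | 148 |

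The widening is √((V + s²)/1.86) − 1, for example √(2.11/1.86) = 1.065.

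**3. Allow correlation.** If the target has correlation c with the follow-up mean given baseline, the variance is V + s² − 2c·s·√V, with √V = 1.364. At s = 0.5 and c = 0.3 this is 2.11 − 0.41 = 1.70, which needs 107 per arm: fewer than 117. Subtracting the target helps once c exceeds s/(2√V), which is 0.11, 0.18 and 0.26 for s = 0.3, 0.5 and 0.7. The table is therefore not a worst-to-best range; the loss can vanish or become a gain.

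**4. Check for bias.** In a simulation with no true effect, 117 per arm, s = 0.5 and targets set independently of arm, the analysis of HbA1c minus target adjusted for baseline alone had mean estimate 0.001 and a false-positive rate of 5%.

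**5. Check the repair.** With the target T as a linear covariate, HbA1c − T and HbA1c differ only by a term already in the model. Only the coefficient of T changes (by 1); the treatment coefficient and the residuals do not. In the simulation the two treatment estimates agreed to within about 1e-14. The variance is then V(1 − c²), which never exceeds 1.86: 117 per arm at c = 0 and 107 at c = 0.3.

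**The case against.** **The endpoint may be deliberate.** Outcomes ties it to an individualized strategy for glycemic control, and distance to a personal goal is a legitimate quantity. Adding the target as a covariate turns the comparison into one of plain HbA1c. This stands as a reason to keep distance to target as a descriptive summary. It does not explain why the objective and sample size are written for HbA1c.

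**The listed covariates already absorb part of the target.** Baseline HbA1c, age, insulin, duration and complications probably predict some of it, which reduces the effective s. This also stands, for the mixed model but not for the t test.

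**A reader might infer bias** from the open-label design and from the statement that investigators "can amend the targets initially predicted at the inclusion visit that patients have to reach over time". The documents do not support this. The amendable targets listed there (The web telemonitoring platform) are steps, blood glucose and weight; HbA1c is not named. Both endpoint definitions use the baseline target. The Intervention section places examination and questionnaires before randomization, and Allocation says enrolling investigators did not know the sequence. The article does not say outright that the HbA1c target is recorded before allocation, but nothing in it says the opposite.

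**A reader might also set the chance imbalance in targets directly against the 0.5-point effect.** At s = 0.5 its 95% limit is 1.96 × 0.5 × √(2/117) = 0.13. That overstates the matter: independent variances add in quadrature, so the half-width goes from 0.35 to 0.37.

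**Conclusion.** The mismatch is real: the objective and sample size concern HbA1c, the endpoint concerns HbA1c minus a target, and the model does not adjust for that target. With a target fixed before allocation, the consequence is possible loss of precision, not systematic bias. For an assumed target SD of 0.3 to 0.7 points unrelated to later HbA1c given baseline, power is about 78% to 70% instead of 80%. The loss is smaller, or becomes a gain, if target and later HbA1c are positively correlated.

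These figures rest on the plan's own SD and correlations, on an assumed target SD, and on the four-visit mean that the sample size uses. The point is worth correcting mainly because the correction is nearly free.

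**What to change.** 1. Add the baseline target HbA1c as a linear covariate in the primary mixed model. The treatment estimate is then the same for HbA1c, for change in HbA1c and for HbA1c minus target, so objective, endpoint and sample size agree. This applies to the mixed model only; an unadjusted t test on the difference still carries the variation in targets.
2. State that the target used is the one recorded before randomization. This rule matters in its own right: adjusting for a target set after allocation would not remove bias if that target is also related to the outcome.
3. Word objective and endpoint alike, for example as 1-year HbA1c compared between arms, adjusted for baseline HbA1c and baseline target. Distance to target can still be reported descriptively.

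The cost is one covariate (one degree of freedom), one sentence on timing and a change of wording. The endpoint already requires the target to be collected, and the stated 117 per arm need not rise.
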